## Abstract

**Background:**

With the widespread use of orally administered anticancer agents, self-management by cancer patients is inevitable, and adherence to medication is becoming the centre of interest in oncology.

**Methods/Design:**

This mixed-method study is a two-phased approach with a combined quantitative and qualitative design. In the first phase, we will conduct a prospective randomised controlled study to assess the effects of a nurse-led medication self-management programme for patients receiving oral anticancer treatment. Patients with metastatic breast cancer, who have been newly prescribed an oral chemotherapy or a targeted therapy agent will be enrolled in the study. The participants will be randomly assigned to either the medication self-management support programme group (intervention group) or the conventional care group (control group). This will be an open-label study; therefore, neither the patients nor the nurses will be blinded. Nurses will provide patients in the intervention group with information by using the teach-back method, help patients set a goal based on their preferences, and solve problems through follow-up counselling. The primary outcome measure is adherence to medication, to be measured on the basis of the medication possession ratio (MPR), which is the ratio of the number of days of medication supply to the total days at a specified time interval. We hypothesize that the intervention group will have an MPR of ≥90 % that is significantly higher than that of the control group. Secondary outcome measures include self-efficacy, quality of life, psychological distress, severity and interference of symptoms, patient satisfaction, emergency department visits, and hospital admissions. In the second phase, we will conduct focus-group interviews with intervention nurses, and perform a content analysis to understand their role and challenges these nurses will face in the programme while improving patients’ medication adherence.

**Discussion:**

The present study will be the first Japanese study to evaluate the effects of medication self-management support provided by nurses to patients with metastatic breast cancer who are receiving oral anticancer treatment. The study is characterised by a unique patient-centred approach aiming to help patients manage their medication based on their needs and preferences, with both quantitative and qualitative evaluations. The findings will contribute to the facilitation of medication management in cancer patients.

**Trial registration:**

UMIN Clinical Trials Registry (UMIN-CTR), Japan, UMIN000016597. (27 February 2015).

## Background

Metastatic breast cancer (MBC), also referred to as secondary or advanced breast cancer, is defined as breast cancer that has spread to other parts of the body [1]. MBC is currently incurable; however, it can be managed as a chronic disease with appropriate treatment strategies [2]. The systematic treatment options for MBC are endocrine therapy, chemotherapy, and biological (targeted) therapy [3]. The goals of care are to control disease progression, extend survival, optimize symptom management, and enhance the quality of life [3–5]. A previous study suggested that patients with MBC are willing to accept substantial risks of side effects in exchange for potential survival benefits [5].

As oral anticancer agents are becoming more common, a critical shift has occurred from clinic-based healthcare provider-administered management to home-based self-administered management, with patient adherence becoming increasingly important [6]. There are very few studies on adherence to medication in patients with MBC, and the results are inconsistent. Although Figueiredo et al. reported high adherence to capecitabine in patients with MBC [7], Di Bonaventura et al. addressed nonadherent beheviours due to forgetfulness and intolerance of side effects in an internet-based study on multiple anti-cancer drugs [5]. Schulman-Green et al. [8] addressed barriers to self-management in patients with MBC, including symptom distress, difficulty in obtaining information and lack of knowledge about the course of cancer. Cancer survivors have unmet needs concerning personal control (e.g., maintaining autonomy and independence), physical problems (e.g., pain and symptoms), and education/information (e.g., lack of knowledge); breast cancer patients identified more unmet needs than other survivors [9]. Furthermore, anxiety and symptoms of depression increase with the increasing incidence of cancer recurrence [10]. When concerns outweigh necessity beliefs, nonadherence occurs according to the balance theory of the necessity-concerns framework [11, 12]. Because many problems specific to MBC are left unanswered, patients with this disease frequently feel a sense of abandonment and isolation, including feelings of uncertainty [13], a lack of control, and poor emotional functioning [14]. With this background, patients with MBC are at risk of nonadherence to medication.

A systematic review on adherence-enhancing interventions for oral chemotherapy suggested that educational and consultation interventions are promising [15]. The models of concordance and shared decision making have emerged as patient-centred approaches [16]. In concordance, a therapeutic alliance is established between the healthcare professional and the patient through encouraging patients to discuss concerns about medications and preference for treatment and participation in decision making. Similarly, the patient and the healthcare professional share knowledge and experience on the available options to make a decision jointly in shared decision-making. As the needs of MBC patients vary greatly, care and support should be tailored to each individual patient, and the patients are encouraged to participate in the decision-making process [4, 17]. It is critical for healthcare professionals to listen to and understand the patients’ concerns, beliefs, preferences, and expectations, and to confirm their understanding and commitment to the treatment [18]. In terms of the patients’ control over medication management, healthcare professionals should focus on helping the patients uncover important issues, set a goal, and solve any problems [19].

The importance of an individualised approach specific to MBC and respecting the patient’s preferences is emphasised in the international consensus guidelines for advanced breast cancer [3]. Although the subjects of the study were not MBC patients, positive results were reported concerning the effect of patient preference-based interventions on adherence [20] and outcomes [21]. A systematic review of quantitative and qualitative studies revealed that providing written information only is not useful; patients do not value written information about medication and do not want this type of information as a substitute for discussion [22]. Teach-back has been used as an educational strategy for patients with chronic disease. This involves asking patients to repeat the key points of a topic or instruction to ensure their understanding of the information provided by the healthcare professionals [23]. This process helps motivate patients to adhere to medication and self-management [24].

With the increase in oral therapies, nurses need to spend more time focusing on patients’ adherence to medication [25] by providing proactive care [26]. Nurses play an important role in educating patients about their treatment and the management of side effects [27], monitoring adherence by identifying potential barriers and implementing intervention strategies [28], and helping patients recognise when to seek professional help [25]. Compared with adherence to hormone therapy in cancer patients [29–33], adherence to oral chemotherapy and targeted therapy is a relatively new area of research. Two studies have reported the significance of nurse intervention, over the telephone in improving adherence to oral chemotherapy; however, one was a feasibility study and the other was a randomised study with a small sample size [34, 35]. Spoelstra et al. [36] suggested the importance of patient education provided by nurses for promoting adherence and managing symptoms. The effect of an intensified pharmaceutical care, including patient education and consultation, has also been reported for the improvement of adherence to capecitabine chemotherapy in patients with breast or colorectal cancer [37].

Few studies have reported on interventions to improve adherence to oral chemotherapy; moreover, studies about oral chemotherapy specific to patients with MBC are rare. The current study focuses on adherence to oral chemotherapy and targeted therapy in an MBC population. We will highlight teach-back, goal setting based on patient preferences, and problem solving through follow-up counselling by nurses under the concept of concordance and shared decision making. We will also conduct a prospective randomised controlled trial on patient-centred intervention to facilitate medication management in MBC patients at three cancer centres in Japan. We will also perform qualitative evaluations on the programme based on the perceptions of intervention nurses.

### Objectives

The objectives of this study are to determine the effects of a patient-centred medication self-management support programme in patients with MBC undergoing oral anticancer treatment, and to evaluate the programme’s effectiveness based on the perceptions of intervention nurses. We hypothesize that the intervention group will have a medication possession ratio (MPR) ≥90 % that is significantly higher than that of the control group.

## Methods/Design

### Study design

The study is a two-phased mixed-method approach, with a prospective randomized, parallel-group, two-arm, open-label, three-centre study and a qualitative study using a focus-group interview. A summary of the study design is given in Fig. 1.

**Fig. 1 Fig1:**
[figure not shown]
Schema of study design

### Study setting

The study will be conducted at three cancer centres in the greater Tokyo area in Japan: the National Cancer Centre Hospital (600 beds), the National Cancer Centre Hospital East (425 beds), and the Kanagawa Cancer Centre Hospital (415 beds).

#### Phase I: An intervention study

##### Recruitment

Primary physicians will identify a sample of eligible participants from outpatient lists of three cancer centre, and recruitment will be performed by nurse investigators at the outpatient clinics before the commencement of oral chemotherapy. Participants will be eligible for the study if they (i) are 20–90 years of age, (ii) have MBC, (iii) can complete a questionnaire in Japanese, (iv) have been newly prescribed with oral chemotherapy or target therapy medication, (v) can manage their medication without any assistance, and (vi) have been given a prognosis of ≥3 months, as determined by their primary physician. Patients will be excluded if they (i) have cognitive impairment or mental disorder, (ii) have brain metastasis, (iii) are receiving infusion therapy, or (iv) are participants in another study. The nurse investigators will provide research information to those who are interested in the study, and will obtain written consent with their potential participants’ signatures. Then, the nurse investigators will send enrolment forms to a data centre through e-mail. The participants will be enrolled after a final determination of eligibility at the data centre. The target sample size is 200 (100 per arm), and the number of planned patients for recruitment at the three cancer centres　(the National Cancer Center Hospital, the National Cancer Center Hospital East and the Kanagawa Cancer Center) will be 64, 64, and 72, respectively.

#### Phase 2: A Qualitative study

After the phase 1 intervention study, nurse investigators will recruit 5 to 10 intervention nurses from each facility to participate in the phase 2 qualitative study at a research meeting. Detailed written information and oral explanation of the study were given to those who were interested in the phase 2 study. Written consent will be obtained from the participants.

##### Randomisation and blinding

The participants will be randomized to either the medication self-management programme group (intervention group) or the conventional care group (control group) at a 1:1 ratio. The Joint Centre for Researchers, Associates, and Clinicians (JCRAC), an independent, non-profit organisation with extensive experience in conducting clinical trials, will conduct the randomisation by using a computerised random number generator. Randomisation will be stratified according to age (<40 vs. 40≦), treatment regimen (Xeloda vs. Xeloda + Tykerb vs. TS-1), and cancer centre. A database containing patient names will be encrypted and sent to the JCRAC. This is an open-label study; therefore patients, nurses, and investigators will not be blinded.

### Intervention

#### Conventional care

Both the control group and the intervention group will receive conventional care from healthcare professionals at the outpatient clinics in each of the participating cancer centres. This includes i) explanation on oral chemotherapy and physical evaluation during the course of the treatment provided by the physician, and ii) instructions on the medication including procedure, frequency, dose, and the steps to take if the patient overdoses or forgets to take the medicine; and (iii) information and contact details with regards to treatment-related toxicity and emergencies provided by the pharmacist; a leaflet will be provided on commencement of treatment. Outpatient nurses will provide psychological support to patients only on request, and nurses providing conventional care will not be trained for the intervention programme.

#### Intervention protocol

We developed the patient-centred medication self-management support programme to consist of three elements: information giving by using teach-back, patient preference, and follow-up by a nurse under the concept of concordance and shared decision making [16, 38–40]. The goal of the programme is to improve adherence to medication and self-management. In addition to the conventional care, the intervention group will receive two sessions of the patient-centred medication self-management support programme conducted by trained nurses in the clinic at 1 and 2 months after enrolment. Each session will take 20–30 min. In the first session, patients will be asked for feedback, in their own words, on what they understand about the medication information provided by the healthcare professionals. Through repeating back the key points of the instructions, the nurse will help the patient recognize whether he or she understands the information correctly and provide motivation toward medication self-management. The patient and nurse will share information and needs, and set a goal on the basis of the patient’s preferences, to facilitate medication management. In the second session, the nurses will review the patients’ management of their medication, and help them solve any problems concerning medication management. The follow-up counseling is restricted to scheduled appointments.

### Intervention nurses

Three to five oncology nurses specialized in chemotherapy will deliver the intervention at each participating centre. These intervention nurses will have had more than 5 years of experience in chemotherapy and will have agreed to participate in the study. To standardize intervention, a 120-min training workshop programme will be implemented for nurses who will be responsible for delivery of the intervention prior to the study. The training programme will include (i) self-management of oral administration, and the concepts of concordance and shared decision making as a patient-centred approach; (ii) basic knowledge and optimal management of oral chemotherapy and targeted therapy; and (iii) teach back and effective communication skills (Table 1).

**Table 1 Tab1:** Training of intervention nurses

Learning contents
1. Understanding the basic theory of medication self-management of oral anticancer agents, and the concept of concordance and shared-decision making as a patient-centred approach.
a. Self-management theory
b. The concept of concordance and shared-decision making as a patient-centred approach
2. Understanding the basic knowledge and optimal management on oral anticancer agents.
a. Treatment regimen and management of side effects
b. Daily management of anticancer agents
c. Steps to be taken if the patient forgets to take a medicine or overdoses
3. Acquire the teach-back and effective communication skills.
a. Communication skills
b. Teach-back skills
c. Confirmation of the patient’s understanding and provision of essential information
d. How to share and review patient preferences in medication management
Q&A (Total 120 minutes)

### Data collection

#### Primary outcome measure

The primary outcome is adherence to medication at 3 months after the commencement of oral chemotherapy or target therapy, as ascertained from the MPR, which is the ratio of the days of medication supply to the total days at a specified time interval, calculated from the medical chart. An MPR of 0 would indicate that no medication had been taken. In this study, an MPR of 90 % will be considered as indicating good adherence [41]. Medication adherence will also be assessed by the Japanese version of the Morisky Medication Adherence Scores (MMAS-8). MMAS-8 is an eight-item self-reporting measure of medication-taking behaviour [42]. The first seven items have a dichotomous response (yes or no); the eighth item has a five-point Likert scale response. The total score of MMAS-8 ranges from 0 to 8. A higher score represents higher adherence to medication.

#### Secondary outcome measures

A number of secondary outcome measures will also be assessed.

##### Self-efficacy

We will use the Japanese version of the General Self-Efficacy (GSE) Scale to assess self-efficacy [43]. The GSE Scale is designed to assess optimistic self-beliefs to cope with a variety of difficult demands in life; it includes10 items, such as ‘I can always manage to solve difficult problems if I try hard enough’ [44]. The response scale ranges from ‘not at all true’ (1 point) to ‘exactly true’ (4 points), and the response scores of all 10 items will be summed. Higher scores indicate higher perceived general self-efficacy.

##### Quality of life

Quality of life will be measured by using the Japanese version of the Functional Assessment of Cancer Therapy-Breast (FACT-B) [45]. This is a 36-item self-reported questionnaire consisting of four subscales: physical (7 items), family/social (7 items), emotional (6 items), functional well-being (7 items), and Breast cancer (9 items) [46, 47]. A 5-point Likert scale ranging from ‘not at all’ (0) to ‘very much’ (4) is used. Higher scores indicate higher quality of life.

##### Psychological distress (K6)

We will use the Japanese version of the Kessler 6 (K6) to assess psychological distress [48]. The K6 is a self-administered tool used for screening mental health issues by asking 6 questions [49]. Individuals will be asked the frequency of feeling nervous, hopeless, restless or fidgety, so depressed that nothing could cheer you up, that everything was an effort, and worthless, during the last 30 days. A score of 10 or more is used to indicate non-specific serious psychological distress.

##### Symptoms severity and interference

We used the Japanese version of the M.D. Anderson Symptom Inventory to assess perceived symptom severity and interference [50]. This is a multi-symptom patient-reported outcome measures for clinical and research use and applies broadly across cancer types and treatments [51]. There are 13 symptom severity items (pain, fatigue, nausea, disturbed sleep, emotional distress, shortness of breath, lack of appetite, drowsiness, dry mouth, sadness, vomiting, difficulty remembering, and numbness or tingling) and severity is rated on a numerical rating scale, from 0 ‘not present’ (0 points) to ‘as bad as you can imagine’ (10 points) [52].There are 6 symptom interference items (general activity, mood, walking ability, normal work, relations with other people, and enjoyment of life), and interference is rated on a numerical rating scale, from ‘did not interfere’ (0 points) to ‘interfered completely’ (10 points). A component score for both symptom severity and interference will be obtained by taking the average of the two scores. Higher scores represent greater symptom severity and interference.

##### Patient satisfaction

Patient satisfaction of the medication self-management support programme is measured by two questions developed for this study. 1) Are you satisfied with the medication self-management support programme? and 2) Do you want to continue to receive support from healthcare professionals? The five response options range from ‘not at all satisfied’ to ‘extremely satisfied’. A higher score indicates greater satisfaction.

Baseline measures will be assessed at 1 month after the initiation of oral chemotherapy before randomisation. Health service visit, including emergency department visits and admissions will be collected from medical records, and only treatment change (discontinuation/dose reduction/oral chemotherapy free interval) will be described in a case report form. The study uptake rates and compliance with the intervention will be recorded. Table 2 summarises the measures and timings for each measurement.

**Table 2 Tab2:** Measures and timings for measurements

Measure	Questionnaire	Baseline	2 months	3 months
Demographics	Patient Questionnaire	○		
Medication adherence	MPS	○	○	○
	MMAS-8	○	○	○
Self-efficacy	GSE	○	○	○
QOL	FACT-B	○	○	○
Psychological distress	K6	○	○	○
Symptom severity/interference	MD Anderson Symptoms Inventory	○	○	○

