### Sample size calculation

The programme will be considered as effective if the proportion of patients who maintain ≥90 % MPR is significantly higher in the intervention group than in the control group, at the completion of 3 months of oral chemotherapy. Previous studies have assumed that adherence has been achieved if the MPR is 70 % in the intervention group and 50 % in the control group [32, 41]. Prospective power analysis revealed that 93 patients were needed in each group for 80 % power at an alpha level of 0.05. Therefore, we plan to recruit 100 patients in each group, for a total of 200 patients.

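### Patients are randomised about one month into treatment, but the primary MPR is dated from commencement with no stated start to its window, so up to a third of it may precede allocation and dilute the effect

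*Protocol article*

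**What the plan says.** All references are to the protocol article.

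- **Randomisation.** The text above Table 2 says: "Baseline measures will be assessed at 1 month after the initiation of oral chemotherapy before randomisation". Allocation therefore comes no earlier than about month 1 of treatment.
- **Primary endpoint.** Under Primary outcome measure: "The primary outcome is adherence to medication at 3 months after the commencement of oral chemotherapy or target therapy". The MPR is defined there as "the ratio of the days of medication supply to the total days at a specified time interval, calculated from the medical chart". No start day is given.
- **Success criterion.** Sample size calculation compares the proportions keeping an MPR of at least 90% "at the completion of 3 months of oral chemotherapy". Statistical methods repeats the criterion at 3 months, adjusted for the allocation factors.
- **Measurement times.** Table 2 lists the chart-based adherence measure (labelled MPS, read here as the MPR) at baseline, 2 months and 3 months.
- **Recruitment.** Under Recruitment: "recruitment will be performed by nurse investigators at the outpatient clinics before the commencement of oral chemotherapy". Enrolment follows an eligibility check at the data centre.
- **Programme sessions.** Under Intervention protocol, the two sessions are "conducted by trained nurses in the clinic at 1 and 2 months after enrolment".

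**The concern.** The endpoint clock starts at commencement and allocation comes about a month later. If the MPR accumulates over the whole three months, the first month counts towards success or failure although nobody has yet been allocated. Those days follow the same distribution in both arms and pull the two proportions together. The price is power, and so a greater chance of missing a real effect. The month-1 MPR would also be spent as noise in the outcome when it could serve as a baseline covariate.

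The session timing adds a second problem. Sessions are counted from enrolment, the endpoint from commencement, and randomisation from the month-1 baseline. How much of any outcome window follows programme contact depends on what enrolment means, and each reading leaves a difficulty.

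**Working it through.** **1. The plan's own figure.** Inputs from Sample size calculation: 70% versus 50%, 80% power, alpha 0.05 (sidedness not stated; two-sided taken here). The pooled-variance formula without continuity correction is

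n per arm = [1.960·√(2·p̄(1−p̄)) + 0.842·√(p₁(1−p₁) + p₂(1−p₂))]² / (p₁−p₂)²

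With p̄ = 0.60: [1.960·√0.48 + 0.842·√0.46]² / 0.04 = (1.358 + 0.571)² / 0.04 = 93. The stated 93 is reproduced. Power at 100 per arm is Φ[(0.20·√100 − 1.358)/√0.46] = Φ(0.947) = 82.8%. The arithmetic of the plan is sound.

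**2. Share of the window before allocation.** Under a commencement-to-3-month window with randomisation at month 1, the share is 1/3. If the window opens at randomisation, it is 0.

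**3. Effect on power, conditional.** Two assumptions: month 1 has the control distribution in both arms, and 70% versus 50% holds for months 2 and 3. The three-month MPR is then (month 1 + 2 × months 2–3)/3. The protocol gives no MPR distribution, so the result is shown over a range.

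| Model | Difference (points) | Needed per arm | Power at 100 per arm |
|---|---|---|---|
| Linear dilution, 2/3 × 20 (63.3% vs 50%) | 13.3 | 216 | 47.7% |
| Beta MPR, precision 5–20, correlation between periods 0.3–0.9 | 13.5–16 | 147–212 | 48–64% |
| Logit-normal MPR, SD 1–2, correlation 0.3–0.9 | 12–15 | 174–269 | 40–56% |

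For the linear row, p̄ = 0.567 and power = Φ[(0.1333·10 − 1.960·√0.4911)/√0.4822] = Φ(−0.058) = 47.7%. This row is only a rough guide, because the proportion above a threshold need not dilute linearly. The two simulations apply the 90% threshold to the weighted MPR. Together the three give about 12 to 16 points and 40% to 64% power.

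**4. The other reading of the rates.** If 70% versus 50% already describes the full three months, 93 per arm and 82.8% stand. The programme must then produce more than 20 points after randomisation: by linear dilution, 20 ÷ (2/3) = 30 points.

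**5. The clocks side by side.**

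- *Enrolment at recruitment, before commencement.* Session 1, one month after enrolment, falls due around or before the month-1 baseline, and hence around or before allocation.
- *Enrolment at randomisation, about month 1.* Sessions fall at about treatment months 2 and 3. The second coincides with the primary assessment, and month 2 passes without programme contact.

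**The case against.** The strongest reply is that the article nowhere says the MPR accumulates from commencement. The 3-month time point fixes when adherence is judged, not when the window opens. Separate entries at baseline, 2 and 3 months in Table 2 fit interval-specific MPRs as well as a cumulative one, and a journal article may leave exact window days to the full protocol. This stands in part: the cumulative window is an inference. But no part of the article starts the MPR clock at randomisation, and the anchors it does state point to commencement.

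Second, the planning rates are attached to the endpoint at three months, so assigning them to months 2 and 3 creates the power loss. This also stands: the loss is conditional. The article does not say which window the rates describe, and the alternative reading asks more than 20 points of the programme after allocation.

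Third, the first month is balanced in expectation. Correct: there is no bias and no inflation of type I error.

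Three stronger readings are tempting but not supported:

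- *The 20-point difference cannot be attained.* It can, if the effect after randomisation is large enough.
- *Patients with 10 uncovered days in month 1 have already failed.* Ten uncovered days in 90 give 80/90 = 88.9%, but the article states no cap on the MPR, so later surplus supply could restore it. No fixed percentage of such patients can be given.
- *The session schedule is unworkable.* If treatment starts promptly after enrolment at recruitment, baseline, randomisation and session 1 all fall around month 1, which is feasible. The wording simply does not ensure that order.

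**Conclusion.** The point holds in a conditional form. The article fixes randomisation after a month-1 baseline, dates the primary endpoint from commencement, and leaves the start of the MPR window open. On the natural cumulative reading, about one third of the window precedes allocation. If 70% versus 50% refers to the post-randomisation months, the difference falls to about 12 to 16 points and power at 100 per arm from 83% to about 40% to 64%, with the MPR distribution and the correlation between periods assumed. If those rates cover the whole three months, or if the window opens at randomisation, the planned power is unaffected. The harm is possible dilution, not bias, and the sample size arithmetic is correct. The timing anchors need reconciling on any reading.

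**What to change.** 1. **Define the window.** Run the primary MPR from the day of randomisation to 3 months after commencement (about 60 days), with the same 90% threshold. State that 70%/50% refers to this window, and report the MPR from commencement to 3 months as supportive. With those rates applied to it, 93 per arm and 82.8% power at 100 per arm stand. Because start and end use different anchors, both days should be written out, with a rule for supply in hand at randomisation.
2. **Use the month-1 MPR.** Enter the adherence measure that Table 2 already lists at baseline as a covariate beside the allocation factors.
3. **Reconcile the clocks.** State what enrolment means, and align the timing of enrolment, randomisation, sessions and assessments across Recruitment, Intervention protocol, Primary outcome measure and the text of Table 2, so that the order of allocation, sessions and primary assessment is unambiguous.

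The cost is wording in the protocol and analysis plan; no new data are needed. The small downside is a coarser individual MPR: at 90%, a 60-day window tolerates 6 uncovered days (0.10 × 60) against 9 in 90.
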